## Abstract

**Background:**

Treatment non-adherence poses a serious risk to survival and hinders the improvement of tuberculosis (TB) control effectiveness in Inner Mongolia, China. To improve treatment adherence and health outcomes in Inner Mongolia, this study aims to maximize the impact of an electronic monitor and smartphone app (EM program) by developing interventions that optimize the EM program, putting it into practice and evaluating it, and developing scale-up activities of the optimized EM program.

**Methods:**

First, a Consolidated Framework for Implementation Research will be used to assess the implementation of electronic monitors to improve treatment adherence and health outcomes for TB patients in China and identify the facilitators and barriers. Second, we will use the Expert Recommendations for Implementing Change protocol to identify appropriate implementation strategies to optimize the EM program in the Inner Mongolian context. Third, the optimized EM program will be implemented and assessed during a 12-month pragmatic, parallel, cluster-randomized trial in three chosen cities in Inner Mongolia. The treatment adherence of TB patients will be the main result. The secondary outcomes will be TB treatment outcomes as defined by the World Health Organization, including the treatment completion rate, loss to follow-up rate, treatment failure rate, and treatment-related deaths. Based on the RE-AIM framework, the impact of the improved EM program will also be assessed in comparison to standard care for the subsequent secondary outcomes (reach, effectiveness, adoption, implementation, and maintenance).

**Discussion:**

This study will be the first to develop and implement interventions that improve the treatment adherence and health outcomes of TB patients in addition to developing strategic options for the scalability and generalizability of the optimized interventions in remote areas of China and other low- and middle-income countries. All intervention activities will be developed for incorporation into regular TB care, with strong local ownership. Through the trial, we hope to uncover more information about the long-term effects, efficacy, cost-effectiveness, and practicability of our intervention.

**Trial registration:**

ISRCTN15169616. Registered on 29 July 2023.

## Introduction

The second most lethal infectious killer after COVID-19 (above HIV/AIDS) is tuberculosis (TB). One of the most prevalent infectious diseases, TB affects almost one quarter of the world’s population (1, 2) and is the 13th leading cause of death. Despite significant efforts to fight it, TB is still a global and Chinese public health concern. According to a report by the World Health Organization (WHO), 1.6 million people worldwide died from TB in 2022 (1, 2). China has the second-highest TB burden in the world (3). A total of 84,200 new cases of TB were reported in China in 2021, with a 59/100,000 incidence rate (1).

Despite the availability of effective TB medications, treatment non-adherence has been demonstrated (4, 5). This continues to be a major obstacle to improving TB control effectiveness and poses a significant risk to survival (6). Treatment non-adherence is a growing concern given the evidence of its high prevalence, correlation with unfavorable outcomes (such as treatment failure, relapse, and drug resistance), and correlation with rising healthcare costs (6, 7). Due to its low population density, harsh weather, lengthy travel distances, and lack of human resources to support the implementation of directly observed treatment, treatment non-adherence is even worse in Inner Mongolia, China (8). To ensure TB intervention adherence in Inner Mongolia, urgent action is needed.

Electronic medication monitor (EMM) boxes, a type of digital health technology, are a promising tool for enhancing TB patients’ treatment adherence. The EMM box helps TB patients remember to take their medications, but it also alerts health care professionals to potentially dangerous health behavior patterns in time for them to take appropriate action before treatment is interrupted or fails (9). It can be connected to TB patients’ smartphones to provide additional alerts and notify caregivers right away about their medication behavior histories, providing them with prompt support if treatment adherence is interrupted and incorrectly recorded (9–11). This addresses the shortcomings of directly observed treatment, video-observed treatment (VOT), and short messaging service, providing TB patients with more convenient and adaptable visual and audible reminders for taking their medications, as well as more individualized follow-up, prescription, and consultation (12, 13).

Most of the current literature focuses on the benefits, effectiveness, cost-effectiveness, robustness, acceptability, feasibility, and usability of electronic monitors to enhance TB patients’ treatment adherence and health outcomes (14–19). Little information exists on how to determine the best course of action and solutions based on problems that TB patients face. Furthermore, to the best of our knowledge, little research has been performed on implementation strategies to produce data that can be generalized and used to guide future scale-up in remote regions of China and other low- and middle-income countries (LMICs).

Implementation research seeks to understand what functions in actual settings, for whom, and under what conditions (20). Theory-based implementation strategies are becoming more popular. Additionally, there is a growing understanding of the necessity of using framework-based approaches to understand the factors that contribute to the success of a program or intervention (21). Future research on the electronic monitor can be greatly improved by implementation research. In 2021, Inner Mongolia began using an electronic monitor and smartphone app (EM program). Therefore, determining how to maximize the EM program’s impact is crucial to enhance treatment adherence and health outcomes in Inner Mongolia. The EM program should be optimized after the successful initial phase, considering the requirements in response to the barriers and facilitators of implementing electronic monitors in the real-world setting. This study will generate a context-sensitive, evidence-based implementation strategy for this optimization in collaboration with Chinese Center for Disease Control and Prevention (China CDC) and Inner Mongolia CDC, with the goal of enhancing the reach, effectiveness, adoption, implementation, and maintenance of the EM program in Inner Mongolia from a multidisciplinary research perspective.

## Methods and analysis

The Standards for Reporting Implementation Studies guidelines were followed when reporting this protocol (see Supplementary Data Sheet 1 for details) (22).

### Study objectives

By maximizing the EM program’s implementation, the overall objective is to improve the treatment adherence and health outcomes of TB patients. The study’s specific goals include:

To identify the barriers and facilitators of implementing EM program that aim to improve TB patients’ treatment adherence and health outcomes in Inner Mongolia, China.To co-produce context-sensitive, and evidence-based interventions that optimize the EM program, and implement the optimized interventions, and evaluate the implementation strategies regarding acceptability, cost-effectiveness, and long-term effects in remote areas of China.To develop strategic options for the scalability and generalizability of the optimized interventions.

### Study design

The optimized EM program’s implementation and evaluation under the theory of implementation science are synthesized in the study’s theoretical model (Figure 1). To improve TB patients’ treatment adherence and health outcomes in China, the EM program will be implemented. The Consolidated Framework for Implementation Research (CFIR) framework will be used to identify the facilitators and barriers to this (23). The Expert Recommendations for Implementing Change (ERIC) protocol will then be used to determine the best implementation strategies for the EM program in the context of China’s remote regions (24). The implementation strategies will be assessed in terms of implementation outcome, service outcome, and patient outcome using the RE-AIM framework (25). The implementation and efficacy of the optimized EM program will be assessed using these indicators, which include reach, effectiveness, adoption, implementation, and maintenance, based on the theoretical model. Figure 1.

**Figure 1 fig1:**
[figure not shown]
Theoretical model for this study.

### Project activities

#### Phase 1: CFIR-based implementation determinants

##### Conceptual framework

We will employ a framework-based implementation research insight approach to systematically examine, identify, and synthesize the facilitators and barriers to implementing EM programs that are meant to increase treatment adherence and health outcomes in TB patients. One of the most widely used and operationalized frameworks for predicting or explaining implementation effectiveness barriers and facilitators is the CFIR (26). Intervention characteristics, outer setting, inner setting, individual characteristics, and process are the five main domains of CFIR, made up of 39 sub-domains. These 39 sub-domains affect the implementation process and outcomes. This framework creates a structured and methodical way to evaluate the environment in which implementation takes place by integrating constructs from published theories and models (27). It might serve as a good starting point for developing multifaceted implementation strategies to increase the uptake, usefulness, and longevity of electronic monitors (28).

##### Study participants

The three groups of participants will be (1) EM program managers, coordinators, and staff; (2) community health center and township leaders and public health staff; and (3) patients and their family supporters during treatment.

##### Data collection and analysis

A semi-structured interview will be used to gather the data. To create the interview guide and direct data collection, we will use the CFIR. Each sampling site will host in-depth interviews. We will consult the managers and staff at each site to determine which employees are best suited for an interview. We will obtain informed consent forms. At each site, interviews will take place over the phone or in person and last for 60 to 90 min. We will take notes and record the interviews. Using a codebook available on the CFIR website (29), two researchers will independently code the recordings and notes from the first three sites to the CFIR framework’s constructs. To prioritize the 39 sub-domains, we will conduct an Analytic Hierarchy Process (AHP) with 10 local implementers. Weight allocation is based on expert consensus through the Delphi method, supported by the following theoretical and practical considerations: (1) Modifiability - Theoretical basis: Following the “modifiability principle” in implementation science, we prioritize intervention points with the highest cost-effectiveness. Practical significance: In resource-limited rural areas, low-cost improvement measures are more sustainable for promotion. (2) Impact – Theoretical basis: Adhering to the “maximum impact principle” to concentrate resources on addressing the most significant barriers to treatment adherence. (3) Resource Intensity – Theoretical basis: Grounded in “resource adaptation theory,” considering the actual implementation capacity of the Inner Mongolia region. Practical significance: Ensuring implementation strategies match local health resource allocation. (4) Time Sensitivity – Theoretical basis: Based on “urgency stratification” to identify implementation barriers requiring immediate attention. Participants will perform pairwise comparisons of sub-domains to construct judgment matrices. Eigenvector methods will derive final weights, with consistency ratios < 0.1 serving as a statistical verification tool to ensure logical consistency of judgments, while the weight allocation itself is founded upon in-depth analysis of implementation science theories and local practical conditions. Expert consensus will be developed through a two-round Delphi process: Round 1: Ten local implementers (5 CDC staff and 5 clinicians) independently ranked the importance of each criterion; Round 2‌: The expert panel will discuss and reach a consensus, specifically considering: (1) The geographical particularities of Inner Mongolia (e.g., low population density, pastoral distribution); (2) The specific needs of TB patients (e.g., low literacy rates, linguistic diversity); (3) The carrying capacity of the existing health system. To validate the rationality of weight allocation, we will employ the following methods: (1) Content Validity Test: Three implementation science experts will evaluate the weight allocation scheme for theoretical soundness and practical relevance; (2) Practical Relevance Verification: The weight allocation results will be compared with the practical work experience of Inner Mongolia CDC to ensure alignment with local implementation realities; (3) Sensitivity Analysis: Strategy selection robustness will be tested under different weight combinations to assess the stability of prioritization outcomes.

Results will inform Tier 1 (top 20% weighted) determinants for ERIC strategy matching. Additionally, two researchers will conduct the analysis independently at each stage of coding, indexing, and interpreting and come to a consensus in the event of any disagreement (30). The policy documents, institution reports, and project meeting notes will also be used throughout the study to identify implementation challenges and opportunities, improve the program, and give site staff feedback (31). The qualitative analysis program NVivo 12.0 will be used to examine all interview data. The narrative synthesis of the general characteristics of the included participants will be tabulated and conducted following the findings of the qualitative analysis, and the five domains of the CFIR framework will be used to summarize the common implementation barriers and facilitators of implementing the EM program. Thematic findings from cases with Cohen’s kappa (*κ*) ≤ 0.6 will be analyzed separately to inform Phase 3 RE-AIM evaluation.

#### Phase 2: ERIC-based implementation strategies

We will code the interview and then determine the most effective implementation strategies to address the contextual barriers discovered in phase 1, using a cutting-edge implementation science approach based on the ERIC protocol (32). To contextualize generic CFIR-ERIC recommendations, we will conduct a 2-round Delphi survey with 7 county CDC staff (≥ 5 years’ experience in TB control) and 7 patient representatives, including 4 urban patients (2 low-literacy older adults, 2 young Chinese-speaking patients) and 3 pastoral patients (2 Mongolian-speaking nomads, 1 Chinese-speaking settler). In Round 1, panelists will independently rate all ERIC strategies on feasibility (1–5 Likert) given local geography/climate, cultural appropriateness for nomadic lifestyles, and digital literacy demands. Round 1 ratings will incorporate AHP-derived weights to stratify strategies (e.g., prioritizing high-modifiability/high-impact combinations). Round 2 will involve a consensus meeting to finalize strategies, with *κ*-statistic calculated for inter-panel agreement on strategy retention/drop decisions (*κ* threshold > 0.6) and priority adaptations (e.g., Mongolian audio substitutes for text alerts). We will use the CFIR-ERIC Implementation Strategy Matching Tool v0.53^1^ to choose strategies based on CFIR barriers. The CFIR-ERIC Matching Tool was developed with assistance from implementation experts (*n* = 169) who responded to the survey and chose up to seven implementation strategies they believed would best address each CFIR barrier (33–35). The top row of an output table lists the seven CFIR barriers (condensed to only include solutions with the highest level of support). In the first column is a list of ERIC implementation strategies. The order of the strategies is based on their overall level of support. The phrase “cumulative percent” denotes the degree to which that strategy is supported by all seven CFIR barriers (33). To create more detailed recommendations, we will combine the results of the CFIR-ERIC tool with advice given to us during interviews and found in the literature (32). We will also combine these recommendations with the local context in this study.

##### Setting

To represent the east, central, and western regions of Inner Mongolia, China, the study will be carried out in the cities of Chifeng, Hohhot, and Baotou. We chose these study locations based on the extent to which the EM program has been implemented, the region, the size of the population, the traffic situation, and the program’s representativeness. With a population of 4.04 million and a land area of more than 9,000 km^2^, Chifeng is located in the east of Inner Mongolia. In 2021, its per capita gross regional product (GRP) was RMB 49,069. Hohhot, the capital of Inner Mongolia, is in the region’s center. It has a population of 3.50 million and a GRP of RMB 53,026 as of 2021. With a population of 2.72 million and a land area of over 27,768 km^2^, Baotou is located in the west and had a GRP of RMB 53,026 in 2021.

##### Participants

The study sample will include patients diagnosed with TB in dispensaries following national and international care guidelines (8), who are initiating a standard 6-month chemotherapy regimen at community health centers or township hospitals. Eligible patients must meet the following criteria: aged ≥ 15 years; no speech, mental, visual, auditory, or other communication impairments; ‌and no cohabitating immediate family members (parents, spouse, children) currently enrolled in this trial.‌ Other cohabitation relationships (e.g., friends, distant relatives, roommates) are not excluded.

Immediate family members are defined as parents, spouse, and children. Other cohabitation relationships (e.g., friends, distant relatives, roommates) are not excluded and will be included in sensitivity analyses to assess environmental influences on treatment outcomes.

##### Intervention

Primary care facilities (such as community health centers and township hospitals) will use the intervention. Facilities that are part of the intervention will run the optimized EM program, and those that are not will run the standard EM program. Community health centers and township hospitals had to sign up for the electronic monitors in accordance with the current EM program. Beyond holding the TB medication, the electronic monitors served two purposes. First, they used human voice recordings to remind patients to take their medication on time. Second, they linked a computer with a mobile app to send the history of patient adherence to a cloud-based server (See Figure 2 (8) for details of the operation mode of EM program) (8). The optimized program incorporates three technical isolation measures: (1) Dynamic QR codes (V1-V40 rotation) with geofencing to block cross-cluster device activation; (2) Mandatory bilingual (Mandarin/Mongolian) confidentiality pop-ups triggered upon EMM access‌, combined with monthly WeChat audits via Tencent Cloud OCR scans to detect shared interfaces and with enforced tiered responses from warnings to account suspension; and (3) Cultural isolation through Mongolian-language interfaces and audio prompts blocking operational replication by non-assigned patients. We will incorporate ERIC-based implementation strategies into the current EM program to create an optimized EM program. Figure 2.

**Figure 2 fig2:**
[figure not shown]
The operation mode of EM program.

To address literacy and linguistic barriers in Inner Mongolia, the optimized system incorporates three key adaptations: (1) Pictorial quick-reference cards illustrating device activation, QR code scanning, medication intake confirmation, battery charging, and troubleshooting procedures; (2) Mongolian audio prompts for dose reminders, low-battery alerts, and operational error feedback; (3) Bilingual interface allowing real-time switching between Mandarin Chinese and Mongolian, with icon-based navigation for low-literacy users. These adaptations complement the existing WeChat-based family support system while maintaining all original technical functions of cloud-based adherence monitoring.

##### Outcomes

The primary study hypothesis is that the optimized EM program will result in higher rates of treatment adherence than standard care. As a result, for TB patients, treatment adherence will be the main result. Treatment adherence will be calculated as the percentage of prescribed doses actually taken by the patient each month. The formula is: ‌Treatment Adherence (%) = (Number of doses actually taken / Number of prescribed doses) × 100%‌. For example, if a patient is prescribed 30 doses per month and actually takes 25 doses, their treatment adherence would be (25/30) × 100% = 83.3%. Adherence will be dichotomized as high adherence (≥80% of doses taken) or non-adherence (<80%). The secondary outcomes for TB treatment will be (1) the treatment completion rate, (2) loss to follow-up rate, (3) treatment failure, and (4) death, as defined by the WHO standard definitions (8, 40). Based on the RE-AIM framework, the impact of the optimized EM program will also be assessed in comparison to standard care for the subsequent secondary outcomes (reach, effectiveness, adoption, implementation, and maintenance) (41, 42). For cases with *κ* ≤ 0.6, Phase 1 qualitative findings will inform the “implementation” and “maintenance” RE-AIM domains to address adherence barriers and enhance sustainability. Table 1 provides additional outcome information. Table 1.

**Table 1 tab1:** Outcomes, indicators, and indicator definition by RE-AIM framework.

Outcome	Indicator	Indicator definition
Service outcome	Treatment adherence	Percentage of prescribed doses actually taken each month
Patient outcome	Treatment completion rate	A TB patient who finished treatment without having evidence of treatment failure, but who did not have negative sputum smear or culture results in at least one prior instance or in the final month of treatment, either because the tests were not conducted or the results were not available
	Loss to follow-up rate	A TB patient who did not initiate treatment or whose treatment was interrupted for two consecutive months or more
	Treatment failed	A TB patient who received treatment and had positive results from a sputum smear or culture at month five or later
	Died	A TB patient who passed away before starting treatment or while receiving it, for any reason
Implementation outcome	Reach	Patient-level coverage among all eligible incident TB cases in the catchment area
	Effectiveness	The effects of the improved e-monitoring program on TB treatment outcomes, treatment adherence, and financial outcomes
	Adoption	The proportion of primary-care facilities that formally integrate the optimised EM into routine workflow
	Implementation	Fidelity: extent to which the optimized e-monitoring program is implemented as per the original protocol
		Feasibility: extent to which the optimized e-monitoring program can be implemented in a specific setting
		Outer context: macro-level external factors including social, funding, and leadership
		Inner context: micro-level internal factors including CDC partnership, programmatic staff, feedback, primary care facility, and individual level
	Maintenance	Sustainability of effectiveness: views on maintaining effectiveness from policymakers, directors of CDC and primary care facilities, healthcare providers, and TB patients
		Stakeholders’ satisfaction: satisfaction with the effectiveness and implementation strategy of the optimized e-monitoring program among policymakers, directors of CDC and primary care facilities, health care providers, and TB patients
		Financial sustainability: views on funding and return on investment from policymakers and directors of CDC and primary care facilities
		Institutionalization of interventions: core components that are transferable and require local adaptation for replication in other settings

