### Data collection

Inner Mongolia CDC will regularly gather patient data, such as name, age, gender, education, occupation, diagnosis, and treatment results. The results of sputum smears performed at the fifth and sixth months, as well as information on conversion at the second month, loss to follow-up, and death, will also be recorded as routinely tracked treatment outcomes (8). The treatment adherence data, collected by the electronic monitors and downloaded from the cloud-based database, will be normalized as percentages of prescribed doses to enable standardized comparisons across patients with varying prescription regimens. To ensure that all missed doses are accurately recorded, we will compare the adherence history obtained from e-monitoring devices with pill counts manually collected at the conclusion of each outpatient visit. Cases with *κ* ≤ 0.6 (indicating device-pill count discrepancies) will trigger qualitative interviews to identify root causes (e.g., device tampering, operational errors, non-adherence), and will be analyzed thematically via NVivo 12.0 per Landis and Koch criteria. Adherence data quality will be further ensured through triple validation‌: (1) Monthly unannounced pill counts (10% participants stratified proportionally across Chifeng, Hohhot, and Baotou populations) with a validity threshold of *κ* > 0.8 (SPSS 28.0); (2) Anti-tampering protocols: Randomized audits + 20 × digital microscopy for blister integrity; (3) Tiered corrections: Device recalibration if 0.6 < *κ* ≤ 0.8; data exclusion followed by root-cause analysis if *κ* ≤ 0.6. While cases with *κ* ≤ 0.6 will undergo root-cause analysis and qualitative interviews to identify potential biases, these cases will remain in the primary Intention-to-treat (ITT) analysis with appropriate statistical handling. Finally, data on implementation costs, such as the number of trainees, the trainers’ labor and travel costs, and the price of the EMM boxes and training materials, will be gathered using the researchers’ work logs. We will implement double entry and examine a representative sample to ensure data entry accuracy.

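### Treatment completion, the only favourable TB treatment outcome, excludes finishers with documented negative sputum, so the best-verified successes fall in no outcome and count as non-events

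*Protocol article*

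**What the plan says.** The Outcomes section of Phase 3 lists four TB treatment outcomes by number: "1) the treatment completion rate, (2) loss to follow-up rate, (3) treatment failure, and (4) death, as defined by the WHO standard definitions". The Abstract (Methods) names the same four. Neither place names cure or treatment success.

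Table 1 then defines each one. Treatment completion is "A TB patient who finished treatment without having evidence of treatment failure, but who did not have negative sputum smear or culture results", continued by "in at least one prior instance or in the final month of treatment", with the reason given as "either because the tests were not conducted or the results were not available". Loss to follow-up needs non-initiation or an interruption of at least two consecutive months. Failure needs a positive smear or culture from month five on. Death is "A TB patient who passed away before starting treatment or while receiving it, for any reason".

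The Data collection section treats late sputum testing as routine: "The results of sputum smears performed at the fifth and sixth months" are recorded, together with conversion at month two.

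The Statistical analysis section compares binary outcomes by odds ratio and risk difference. Table 1 also counts TB treatment outcomes under RE-AIM effectiveness.

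The Abstract describes the last two outcomes as "treatment failure rate, and treatment-related deaths", which is a narrower death outcome than the one in Table 1.

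**The concern.** As worded, completion is a residual class: it holds patients who finished but whose negative sputum was never documented. Such a class makes sense beside a cured class, because the two together make up success. Here it stands alone and is the only favourable outcome. A patient with the best-verified result is scored in the same way as a patient who failed, died or was lost.

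Two things are at stake. The completion rate depends on how much sputum testing is recorded as well as on how many patients finish. And a part of each arm, possibly a large part, has no named treatment outcome, so the four rates do not describe the cohort.

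**Working it through.** The article states no expected completion, cure or sputum-testing rate, so there is no figure of the plan's own to reproduce. The check has a logical part and an illustrative part.

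**Classification.** Take a patient who finishes without interruption, with a negative sputum earlier in treatment and another in the final month.

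- Completed: no, because the negatives exist.
- Lost to follow-up: no, because treatment was started and not interrupted.
- Failed: no, because there is no positive result from month five on.
- Died: no.

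No other outcome is named.

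**Two readings of the sputum clause.** The words "in at least one prior instance or in the final month of treatment" can be taken in two ways.

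- Either negative missing: a finisher who lacks one of the two still counts as completed, and only finishers with both documented drop out.
- Both negatives missing: any documented negative removes the patient.

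The fully documented finisher is excluded on both readings. The reading changes how many patients are excluded, not whether the gap exists.

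**Formula.** Let F be the share of an arm that finishes without evidence of failure, and s the share of those finishers whose documented negatives exclude them under the reading chosen. Then

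completion rate = F × (1 − s), and share with no outcome = F × s.

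With subscripts C (control) and I (intervention), the risk difference is

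RD = (F_I − F_C)(1 − s_C) − F_I (s_I − s_C).

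The first term is the true difference shrunk by 1 − s_C. The second is pure documentation bias, and it is zero when s is equal in the arms.

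**Illustration.** All values of F and s are assumptions.

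| F control / intervention | s control / intervention | Completed, control | Completed, intervention | RD (points) | True difference in F |
|---|---|---|---|---|---|
| 85% / 85% | 50% / 50% | 42.5% | 42.5% | 0 | 0 |
| 85% / 90% | 50% / 50% | 42.5% | 45.0% | +2.5 | +5 |
| 85% / 85% | 20% / 30% | 68.0% | 59.5% | −8.5 | 0 |
| 85% / 85% | 50% / 60% | 42.5% | 34.0% | −8.5 | 0 |
| 85% / 85% | 50% / 70% | 42.5% | 25.5% | −17.0 | 0 |
| 85% / 90% | 50% / 60% | 42.5% | 36.0% | −6.5 | +5 |

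For example, row four is 0.85 × 0.40 − 0.85 × 0.50 = 0.340 − 0.425 = −0.085 (odds ratio 0.70). Row six by the decomposition is 0.05 × 0.50 − 0.90 × 0.10 = 0.025 − 0.090 = −0.065.

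**Equal documentation.** A true +5 points becomes 5 × (1 − s): +4.0 at s = 20%, +2.5 at 50% and +1.5 at 70%. With F = 85%, the share of the arm with no outcome is 17.0%, 42.5% and 59.5% respectively.

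**Break-even.** With F = 85% versus 90%, the apparent benefit is gone once s_I exceeds 1 − 0.85(1 − s_C)/0.90. That is 24.4%, 52.8% and 71.7% for s_C of 20%, 50% and 70%. A documentation imbalance of about 2 to 4 points is enough.

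**After the fix.** The combined rate is F × (1 − s) + F × s = F. It equals the true share finishing for every s: a difference of 0 when F is 85% in both arms, and +5 points when F is 85% versus 90%.

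**The case against.** The strongest objection concerns direction. A reader might infer that the optimised programme will improve sputum follow-up and so appear harmful. The article does not support that. The adaptations it describes (pictorial cards, Mongolian audio, a bilingual interface, isolation measures) do not concern sputum testing, and the implementation strategies are still to be chosen. Control facilities also run an electronic monitor programme, and smear results are gathered routinely with no stated difference by arm. A differential is not excluded either, so reversal is a possibility that depends on an assumption. With equal documentation the result is dilution.

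A reader might also infer that any negative result disqualifies a patient. On one natural reading only fully documented finishers drop out. Eligibility is not restricted to bacteriologically confirmed disease and no testing rate is given, so the size of the gap cannot be read from the document. This stands, and it is why ranges are shown.

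Third, the article cites WHO definitions, the Abstract introduces its list with a word that may leave it open, and a fuller document may hold a further category. This carries less weight. The Outcomes section gives a closed, numbered list, and Table 1 writes out the completion definition in full, exclusion included. An analysis that follows the article inherits that numerator. It is still not certain that these patients would go unclassified in practice.

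Finally, this is a secondary outcome. Loss to follow-up, failure and death keep their own definitions, so an odd completion result could be noticed against them. That limits the damage but does not make the completion rate interpretable.

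**Conclusion.** The point holds as a defect in how a secondary outcome is defined. Under either reading of the sputum clause, a finisher with full negative documentation has no named outcome and counts as a non-event for completion. This follows from the text alone.

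The size rests on assumed values. With equal documentation of 50%, a true +5 points is halved to +2.5. With unequal documentation, a 10-point imbalance produces −8.5 points and a 20-point imbalance −17 points when there is no true difference and 85% finish in both arms. Certain harm or a certain change of sign is not shown, because nothing in the document says that documentation will differ by arm.

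The defect affects the comparison of treatment completion and the treatment-outcome part of RE-AIM effectiveness. The primary adherence outcome and the sample size do not depend on it. The mismatch between the Abstract and Table 1 on death is a separate, minor conflict of wording.

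**What to change.** Add to Table 1 a category for patients who finish without evidence of failure and have documented negative sputum, and state which reading of the prior-or-final-month clause separates it from completion. Every patient who finishes without failure then falls in exactly one of the two.

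For the comparison between arms, use the combined proportion: all who finished without evidence of failure, with or without documented negative sputum, over all randomised patients. Show the two components by arm descriptively, so that any difference in sputum documentation is visible.

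Reconcile the Abstract with Table 1 on whether death means treatment-related death or death from any cause.

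The cost is small. The Data collection section already covers treatment results, month-five and month-six smears, month-two conversion, loss to follow-up and death, so no new data are needed. The downside is an outcome amendment in a trial that, by its own timeline section, has recruited since January 2023. It should go through the steering committee, which Trial management names for significant protocol changes, and be dated before outcomes are compared by arm.
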